### **3.1.3 High-risk Patients for CKD**

#### **3.1.3.1 Inclusion Criteria**

1. Age  $\geq 18$  years

2. No established diagnosis of CKD

3. Presence of at least one of the following risk factors:

(1) Type 2 diabetes mellitus (T2DM) (ICD-coded)

(2) Hypertension (ICD-coded)

(3) Cardiovascular disease (ICD-coded)

(4) Obesity: body mass index (BMI)  $\geq 28.0 \text{ kg/m}^2$  per Chinese expert consensus, or relevant ICD-10 codes.

(5) History of AKI/AKD: meeting either KDIGO SCr criteria or a clinical diagnosis, as detailed in **Table 3**

(6) Kidney stones (ICD-coded)

(7) Family history of kidney disease

(8) Advanced age ( $>60$  years)

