### 3.2.1 CDSS

The CDSS will be developed using a Plan-Do-Check-Act framework and will be integrated into the existing EHR system. In the Plan phase, semi-structured interviews with PCPs will be conducted to identify user needs. The Do phase will involve a multidisciplinary team (including nephrologists, technical experts, and PCP representatives) in designing an initial prototype. A pilot study at an independent primary care center will then be conducted as the Check phase, during which the system will be iteratively refined. Finally, the Act phase will consist of evaluating the system's effectiveness and implementation feasibility through the main clinical trial described above. The CDSS is designed to provide non-intrusive, real-time clinical decision support during patient encounters. The key functionalities deployed in the intervention arm include:

1. Automated case identification & risk stratification: The system automatically identifies patients with or at risk of CKD through structured diagnostic codes and laboratory data.

2. Renal referral for patients without prior diagnosis of CKD

- (1) Rapid decline in renal function meeting the AKD criteria (**Table 3**).

- (2) Presence of refractory hypertension: defined as blood pressure (BP) >140/90 mmHg while prescribed  $\geq 3$  antihypertensive medications, or being prescribed  $\geq 4$  classes of antihypertensive medications.

- (3) Persistently proteinuria, hematuria or eGFR <60 mL/min/1.73m^2 (two consecutive abnormal results obtained  $\geq 90$  days apart)

3. Automated CKD staging (stages 1-5)

4. Structured management protocols for diagnosed CKD patients:

- (1) Stage-specific monitoring of renal function (e.g., eGFR, UACR every 3 month).

- (2) Complication management alerts for identification, evaluation and management targets based on thresholds defined as follows: hypertension (BP >130/80 with proteinuria or >140/90 without), CKD-mineral and bone disorder (CKD-MBD) (corrected Ca2+ <2.2 mmol/L; PO4 >1.61 mmol/L), hyperkalemia (K+ >5.5 mmol/L), metabolic acidosis (pH <7.25 or HCO3 <22 mmol/L), anemia (Hb <120 g/L [Male] / <110 g/L [Female]), and dyslipidemia (LDL-C >1.8 mmol/L).

5. Renal referral for CKD patients presenting with following indications:

- (1) Advanced CKD (stage 4-5)

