### **3.3.2 Secondary Outcomes**

- 
1. Changes in CKD diagnosis rate: the difference in the proportion of CKD patients with an ICD-code for CKD documentation between the follow-up and baseline periods.
  2. Changes in utilization of renoprotective medications: the difference in prescription rates of RAASi and SGLT2i among CKD patients between the follow-up and baseline periods, reported separately.
  3. Changes in screening rate for CKD: the difference in the proportion of patients at high risk for CKD who complete SCr and/or urine protein testing between the follow-up and baseline periods.
  4. Changes in renal referral rate: the difference in the proportion of CKD patients meeting criteria for nephrologist consultation referral who are actually referred.
  5. Changes in blood pressure control rate: the difference in proportion of CKD patients achieving a target of <130/80 mmHg, based on available tests.
  6. Changes in glycemic control rate: the difference in the proportion of CKD patients achieving a HbA1c <7%, based on available tests.
  7. Changes in lipid control rate: the difference in the proportion of CKD patients achieving a LDL-C <2.6 mmol/L, based on available tests.
  8. Cost-effectiveness of the CKD-CDSS: economic evaluation of the community-based CKD screening and management program.
  9. CDSS implementation process: process evaluation using the RE-AIM framework (**Table 5**) to understand the implementation of this complex intervention. This evaluation examines the factors influencing outcomes across five dimensions—Reach, Effectiveness, Adoption, Implementation, and Maintenance—at both the individual and organizational levels. An initial phase, structured questionnaires for community institutions and physicians (**Table 6**) will be used to inform the timely optimization of the CDSS and its implementation strategy.

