|                        | Beijing          | E11.901                                                                                                                                                                                                                                                                                                                                                                                                                                                                                                                                                                                                                                    |
| Hypertension           | WHO              | I10, I11, I12, I13, I15                                                                                                                                                                                                                                                                                                                                                                                                                                                                                                                                                                                                                    |
|                        | China            | I12.900x003, I13.900, I10.x00x002, I12.900, I10.x00, I11.900, I10.x09, I15.900, I11.901                                                                                                                                                                                                                                                                                                                                                                                                                                                                                                                                                    |

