|                        | Beijing          | I13.901, I10xx11, I10xx02, I12.903, I15.901, I11.901                                                                                                                                                                                                                                                                                                                                                                                                                                                                                                                                                                                       |
| Cardiovascular Disease | WHO              | G45, I22, I48, I63/I64, I20, J81, I11.9, I50.0, I24, I61, I11.0, I48.0, I50, I25.103, I50.1, I23, I60, I48.1, I64, I13.0, I51.6, I48.2, I25, I21                                                                                                                                                                                                                                                                                                                                                                                                                                                                                           |
|                        | China            | I50.000, I21.900x017, I48.000, I50.904, I61.900, I50.100, I11.000, I48.100, I50.905, I50.000x006, I50.103, I50.900x018, I48.x00x015, I11.001, I48.200, I48.x01, I64.x00, I48.900x004, I50.104, I21.900, I50.105, I48.100x002, I20.900, I50.901, I50.900x007, I50.900x002, I11.002, I50.101, I48.x02, I50.902, I24.800, I13.000, J81.x00x002, I23.800, I50.102, I50.900x008, I48.x00x009, G45.900, I50.001, I50.907, I50.900x017, I25.103, I48.x00, I60.900, G45.900x001, J81.x00, I50.100x006, I50.002, I48.x00x023, I50.900, I25.900, I50.903, I48.x00x011, I50.900x009, I50.000x005, I11.900, I48.100x003, I50.908, I50.900x010, I51.600 |

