|                        | Beijing          | N20.003, N20.201, N20.901, N20.101, N20.000y003, N20.005, N20.902                                                                                                                                                                                                                                                                                                                                                                                                                                                                                                                                                                          |
| CKD                    | WHO              | N18.916, N18.917, N18.915, N18.914, N18.918                                                                                                                                                                                                                                                                                                                                                                                                                                                                                                                                                                                                |
|                        | China            | N18.803, N18.400, N18.200, N18.804, N18.500, N18.300, N18.801, N18.802, N18.001, N18.100                                                                                                                                                                                                                                                                                                                                                                                                                                                                                                                                                   |

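### Table 2 treats I12 and I13 only as hypertension or cardiovascular codes, so patients with a recorded kidney disease can enter the high-risk cohort for main outcome 2

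*Protocol*

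**What the plan says.** Section 3.1.1 of the protocol refers the reader to Table 2 for the ICD codes behind the inclusion and exclusion criteria. The relevant rows are:

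- Hypertension, WHO: "I10, I11, I12, I13, I15".
- Hypertension, China: "I12.900x003, I13.900, I10.x00x002, I12.900, I10.x00, I11.900, I10.x09, I15.900, I11.901".
- Hypertension, Beijing: "I13.901, I10xx11, I10xx02, I12.903, I15.901, I11.901".
- Cardiovascular disease, WHO, closing part of the list: "I64, I13.0, I51.6, I48.2, I25, I21". The local forms I13.000 (China) and I13.001 (Beijing) stand in the same block.
- CKD, China: "N18.803, N18.400, N18.200, N18.804, N18.500, N18.300, N18.801, N18.802, N18.001, N18.100". The WHO and Beijing CKD lists have five codes each, all N18.

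Section 3.1.2.1 admits a patient to the CKD cohort by a confirmed pair of low eGFR values, by a confirmed pair of positive proteinuria results, or (criterion 3) by a CKD code plus one qualifying result. Section 3.1.3.1 admits a patient to the high-risk cohort on two conditions besides age: "No established diagnosis of CKD", and at least one risk factor. Coded hypertension and coded cardiovascular disease are both on the risk-factor list.

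Secondary outcome 1 (section 3.3.2) is "the difference in the proportion of CKD patients with an ICD-code for CKD documentation between the follow-up and baseline periods". It cites no code list.

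**The concern.** A code whose title names renal disease counts towards hypertension and nowhere towards CKD. The two cohorts carry the two main outcomes in section 3.3.1: kidney or cardiovascular hospitalisation in CKD patients, and kidney-related hospitalisation in high-risk patients. A code list that sends recorded kidney disease to the second cohort moves patients between the two main-outcome populations. It also blurs what main outcome 2 measures, which is meant to be kidney events in people not yet diagnosed with CKD.

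A second, weaker question concerns secondary outcome 1. If the same N18-only list is used there, a laboratory-confirmed CKD patient whose physician recorded I12 or I13 would count as undocumented, and a later change to N18 would count as a gain.

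**Working it through.** No figure in the plan needs reproducing. The check compares the code lists and then follows a patient through the rules.

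**Code lists (Table 2).** I12/I13 entries in the hypertension row: WHO 2 of 5, China 3 of 9 (I12.900, I12.900x003, I13.900), Beijing 2 of 6 (I12.903, I13.901). N18 entries in the CKD row: WHO 5 of 5, China 10 of 10, Beijing 5 of 5. No code is shared between the two rows. The WHO CKD list repeats the Beijing list exactly, so the CKD row needs checking in any case.

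**Routing.** Compare a patient coded N18 with one coded I12 or I13 and no N18, both adult and otherwise eligible.

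| Laboratory record | Coded N18 | Coded I12/I13, no N18 |
|---|---|---|
| (a) Confirmed pair, at least 90 days apart | CKD cohort | CKD cohort |
| (b) One qualifying result, no confirmed pair | CKD cohort by criterion 3 | Fails criterion 3; high-risk through the same code |
| (c) No qualifying result | Not in the CKD cohort; a CKD diagnosis is on record, so not high-risk either | High-risk through the same code |

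Row (c) for N18 reads the absence of an established diagnosis as the absence of a CKD code. That agrees with section 3, where baseline CKD diagnosis is based on ICD codes. Rows (b) and (c) are the misrouting. A patient coded locally as I13.000 or I13.001 takes the same path through the cardiovascular risk factor. Deleting I12/I13 from the hypertension row would not cure this, because such patients may also qualify by age over 60 or another risk factor. The correction has to act on the CKD condition.

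**Size, high-risk cohort.** Let p be the share of that cohort coded I12/I13 without N18, and k their kidney-hospitalisation rate relative to the rest. Their share of events is p·k / (1 − p + p·k). The protocol gives neither p nor k, so no number can be put on it. At k = 1 the share is simply p; it exceeds p only if k exceeds 1.

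**Size, secondary outcome 1 (illustration, assumed inputs).** Let f be the share of CKD-cohort patients with I12/I13 and no N18, and c the share of these later recoded to N18. If the outcome uses N18 only, baseline documentation is lower by f than if I12/I13 counted, and recoding alone adds f × c.

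| f (assumed) | c = 0% | c = 50% | c = 100% |
|---|---|---|---|
| 1% | 0 | 0.5 points | 1 point |
| 5% | 0 | 2.5 points | 5 points |
| 10% | 0 | 5 points | 10 points |

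The range includes zero, and the documents do not narrow it.

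**The case against.** **The listing is not an error in itself.** This stands. Patients coded I12 or I13 are hypertensive and belong in a hypertension covariate. The fault is that the codes count nowhere as a kidney diagnosis.

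**The code titles come from outside the protocol.** This is true, but they are standard ICD-10 nomenclature. It is also fair that the local I12 codes are all I12.9 forms, which state no CKD stage. That makes it debatable whether they are adequate CKD documentation for outcome 1. It matters less for a criterion that asks only whether a diagnosis exists.

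**The remedy is looser than the CKD criteria, where even N18 needs one abnormal result.** This does not stand for the high-risk cohort: section 3.1.3.1 asks for no established diagnosis and requires no laboratory confirmation. For the CKD cohort, the proposal keeps the requirement of one qualifying result.

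**The analysis plan may deal with it.** For outcome 1 this stands: section 3.1.1 ties Table 2 to eligibility, and an outcome code list may properly sit elsewhere. For eligibility it does not, because the protocol has already fixed the list. If the lead-in to Table 2 carries a note assigning I12/I13 to CKD, the point falls; none appears in the table body or in the sections that use it.

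**A reader might infer that the CDSS arm is favoured.** Section 3.2.1 lists "Automated CKD staging (stages 1-5" among the functions deployed in the intervention arm, and staging could prompt N18 codes. But the protocol does not say that the CDSS writes or prompts ICD codes, and both arms receive CKD training from nephrologists (sections 3.2.2 and 3.4.3). Baseline miscoding should be similar across randomised arms, and a move from an unstaged code to a staged one may be part of what objective 1 seeks.

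**Conclusion.** The eligibility point holds. As Table 2 and sections 3.1.1, 3.1.2.1 and 3.1.3.1 stand, a patient with I12 or I13, no N18 and no confirmed pair of results is kept out of the CKD cohort and can enter the high-risk cohort on that same code. This rests on two things: the standard meaning of the codes, and section 3.1.1 making Table 2 the eligibility definition. The number of patients is unknown and can be counted from data already held.

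Three stronger readings are not supported. That patients are scored as undiagnosed in secondary outcome 1 is an inference, since that outcome names no code list. That recoding favours the CDSS arm is possible, not shown. That these patients supply a large share of kidney events in the high-risk cohort has no figure behind it; the cohort is broad, and their contribution may be small.

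**What to change.** 1. In the high-risk criteria, treat I12 and I13, including I13.0 and its local forms, as a recorded kidney diagnosis, so that these patients leave the high-risk cohort.
2. In CKD criterion 3, accept I12 or I13 plus one qualifying result on the same terms as N18.
3. Keep I12 and I13 in the hypertension covariate.
4. For secondary outcome 1, name the code list. N18 only may remain the main definition; add a sensitivity analysis that counts I12/I13 as kidney disease documentation at both baseline and follow-up, which shows how much of any gain is recoding.
5. Count, by arm and laboratory route, the screening-period patients coded I12/I13 without N18, and check the WHO CKD entries.

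The cost is a code-list edit, one re-run of the cohort query and one extra analysis. The high-risk cohort becomes slightly smaller, and the CKD cohort gains the patients in row (b).

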#### 3.1 Research Subjects

##### 3.1.1 Study Population

The study population comprise adult patients managed across 30 community health centers in Xicheng District, Beijing (**Table 1**). To ensure sufficient data for follow-up, patients were selected from all visits to these centers during a one-year screening period (March, 10, 2022 – March, 10, 2023), with the inclusion criterion of having at least two visits during this period. The study is primarily focused on CKD patients, while analysis will include a cohort of high-risk population for developing CKD. ICD codes for defining diseases in study population inclusion/exclusion criteria are summarized in **Table 2**.

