|                        | Beijing          | I60.901, I25.105, J81xx01, I50.904, I50.905, I48xx15, I50.004, I50.103, J81xx02, I13.001, I48xx04, I11.001, I20.902, I50.106, I48xx02, I48xx08, I50.910, I50.006, I50.003, I21.902, G45.901, I50.902, I48xx13, I50.102, I48xx07, I48xx06, I50.107, I50.001, I50.907, I50.005, I50.909, I64xx02, I11.901, I64xx04, J81xx03, I50.917, I50.908, I48xx14, I48xx09, I50.911, I50.104, I48xx11                                                                                                                                                                                                                                                   |
| Acute Kidney Injury    | WHO              | N17, N01, T79.5, D59.3, K76.7, O90.4, O08.4, N99.0                                                                                                                                                                                                                                                                                                                                                                                                                                                                                                                                                                                         |
|                        | China            | N10.x00, N10.x01, N00.900x009, N10.x00x003, N12.x00x005, N17.001, N00.951, N00.901, N13.801, N17.251                                                                                                                                                                                                                                                                                                                                                                                                                                                                                                                                       |

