|                        | Beijing          | N00.908, N10xx03, N10xx04+H20.9                                                                                                                                                                                                                                                                                                                                                                                                                                                                                                                                                                                                            |
| Obesity                | WHO              | E66.8, E66.2, E66.1, E66.9                                                                                                                                                                                                                                                                                                                                                                                                                                                                                                                                                                                                                 |
|                        | China            | E23.609, E23.605, E23.600x016, E66.100x001, E66.800, E66.100, E66.801, E66.901, E66.200x001, E66.900, E66.200                                                                                                                                                                                                                                                                                                                                                                                                                                                                                                                              |

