| SCr diagnostic criteria for AKI/AKD | 
meet any one of the following conditions:
 
 
○ SCr rises <math>\geq 26.5 \mu\text{mol/L}</math> within 48 hours
 
○ SCr decreases by <math>\geq 26.5 \mu\text{mol/L}</math> within 48 hours
 
○ SCr rises by 50% within 7 days
 
○ SCr decreases by 50% within 7 days
 
○ SCr rises by 50% within 7 to 30 days
 
○ SCr decreases by 50% within 7 to 30 days
 
○ eGFR rises by 35% within 3 months
 
○ eGFR decreases by 35% within 3 months
 
○ The current eGFR is less than <math>60 \text{ ml/min/1.73m}^2</math> and the eGFR within 3 months is greater than <math>60 \text{ ml/min/1.73m}^2</math>
 
○ (Extended criteria) SCr increased or decreased by <math>> 50\%</math> compared with baseline creatinine (baseline creatinine is defined as the median creatinine within 8-365 days)
 
 |
| ICD -10 code for AKI/AKD            | 
 
○ WHO ICD-10 code: N17, N01, T79.5, D59.3, K76.7, O90.4, O08.4, N99.0
 
○ China ICD-10 code: N10.x00, N10.x01, N00.900x009, N10.x00x003, N12.x00x005, N17.001, N00.951, N00.901, N13.801, N17.251
 
○ Beijing ICD-10 code: N00.908, N10xx03, N10xx04+H20.9
 
                                                                                                                                                                                                                                                                                                                                                                                                                                                                                                                                                                                               |

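### The WHO, China and Beijing code rows for AKI, type 2 diabetes and cardiovascular disease do not select the same patients, and no rule says how the rows combine or match

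*Protocol*

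**What the plan says.** Section 3.1.1 gives the purpose of Table 2: "ICD codes for defining diseases in study population inclusion/exclusion criteria are summarized in" that table. Each of the three diseases has a WHO, a China and a Beijing row.

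- **AKI.** WHO: "N17, N01, T79.5, D59.3, K76.7, O90.4, O08.4, N99.0". China: "N10.x00, N10.x01, N00.900x009, N10.x00x003, N12.x00x005, N17.001, N00.951, N00.901, N13.801, N17.251". Beijing: "N00.908, N10xx03, N10xx04+H20.9". Table 3 repeats all three lists under the label AKI/AKD; its last entry reads "Beijing ICD-10 code: N00.908, N10xx03, N10xx04+H20.9". The agreement between the two tables makes a fault in text extraction unlikely.
- **Type 2 diabetes.** WHO: E11. China: E11.900. Beijing: E11.901.
- **Cardiovascular disease.** The WHO row begins "G45, I22, I48, I63/I64, I20, J81, I11.9, I50.0, I24, I61" and the China row begins "I50.000, I21.900x017, I48.000, I50.904, I61.900, I50.100, I11.000, I48.100". The Beijing row is a separate local list.

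Section 3.1.3.1 makes type 2 diabetes, cardiovascular disease and a history of AKI/AKD three of the eight risk factors, any one of which admits a patient to the high-risk cohort. Section 3.6.2.1 names diabetes and cardiovascular disease among the adjustment covariates.

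**The concern.** A reader who meets three coding versions of one disease expects three ways of finding the same patients. Here the China and Beijing AKI rows consist mostly or wholly of categories that the WHO row does not contain. The local diabetes and cardiovascular rows are narrower than the WHO row. Nothing in the protocol says whether a record is checked against its own version's row or against all three, or whether a listed code stands for itself or for everything beneath it.

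Two programmers following the protocol could therefore produce different high-risk cohorts, different diabetes and cardiovascular covariates and different AKI/AKD histories from the same data.

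**Working it through.** There is no stated figure to reproduce. The check compares the three-character categories in each row of Table 2.

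| Disease | WHO-row categories | Also in China row | Also in Beijing row | Local categories not in WHO row |
|---|---|---|---|---|
| AKI | 8 | 1 (N17) | 0 | China: N00, N10, N12, N13; Beijing: N00, N10 |
| Cardiovascular disease | 17 | 15 (not I22, I63) | 11 (not I22, I23, I24, I51, I61, I63) | none |
| Type 2 diabetes | 1 (E11) | 1, as one code | 1, as one code | none |
| Hypertension, for comparison | 5 | 5 | 5 | none |

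**AKI, by code.** Two of the 10 China codes (N17.001 and N17.251) lie in a WHO-row category. The other 10 − 2 = 8 are N00, N10, N12 or N13 codes. None of the 3 Beijing codes lies in a WHO-row category.

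**Cardiovascular disease.** The China row misses 17 − 15 = 2 categories and the Beijing row 17 − 11 = 6. The WHO row lists I51 only as I51.6, so that is the gap in Beijing. These counts are at category level. Within a shared category the local row may hold very few codes (the China row has one I20 code, the Beijing row one I21 code), so under exact matching the gap is larger than the category count shows.

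**Hypertension** shows that the rows can be aligned at category level: all five categories appear in all three rows.

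**What follows under each reading:**

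1. *Each record matched exactly to its own row.* A China- or Beijing-coded record with any E11 code other than the one listed is not flagged as type 2 diabetes. Local I22 and I63 records, and Beijing I23, I24, I51.6 and I61 records, are not flagged as cardiovascular disease. A Beijing-coded N17 record is not flagged as AKI by its code and is found only if the creatinine/eGFR criteria or the text search in Table 3 catch it. The listed Beijing N00 and N10 codes do count.
2. *Rows pooled, matching exact.* Local E11 codes other than .900 and .901 are still missed.
3. *Rows pooled, matching by prefix.* E11 captures every local E11 code, and the WHO cardiovascular entries capture the missing local categories, so both diseases are repaired. The AKI/AKD set then holds the WHO categories plus the N00, N10, N12 and N13 codes, and is wider than the WHO row. The creatinine and text routes can add patients but cannot remove those admitted by these codes.

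**Size for diabetes under reading 1.** If f is the share of locally coded diabetic patients who carry only other E11 codes, the flag's sensitivity is 1 − f. The protocol gives no value for f, so no percentage is attached here.

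**The case against.** The strongest reply is that the protocol never says the rows must be equivalent or must be applied separately. The table has marks of a pooled list: the WHO and Beijing rows for CKD are identical, the WHO cardiovascular row contains I25.103, which is also in the China row, and the local obesity rows add E23 codes that the WHO row lacks. Sections 3.5.1 and 3.5.2 also plan standardised diagnosis coding and dictionary normalisation. This stands in part. Pooling by prefix does repair diabetes and cardiovascular disease, so misclassification is conditional on the reading. But the pooling rule is not written down, and no reading makes the three AKI rows agree.

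For AKI, the entry criterion is a history of AKI **or AKD**, so broader acute kidney codes may be intended. That is plausible. It would mean the WHO row is too narrow rather than the local rows too wide, and the disagreement remains. The creatinine/eGFR and text-search routes do reduce missed cases.

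Four stronger inferences are tempting and are not supported:

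- *The diabetes and cardiovascular rows name different conditions.* They do not. Every local category lies within the WHO row, so those rows are narrower. Both local cardiovascular rows also carry I64 codes, so stroke coding is not absent.
- *A diabetic subgroup analysis is damaged.* None is specified. Objective 6 in Section 2.2.2 refers to diabetic kidney disease, but outcome 6 in Section 3.3.2 is measured in CKD patients, and nothing says the E11 codes define diabetic kidney disease.
- *The main outcomes will miss AKI or stroke admissions.* Section 3.1.1 ties Table 2 to inclusion and exclusion. No section applies it to hospitalisations, and outcome code lists may sit in a SAP that is not shown.
- *The treatment comparison is biased.* Section 3 takes baseline characteristics from the screening period before the intervention, and unadjusted estimates will also be reported.

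**Conclusion.** The point holds in a limited form. The AKI rows disagree outright (Beijing 0 of 3 codes and China 2 of 10 codes in a WHO-row category), in Table 2 and again in Table 3. The local diabetes and cardiovascular rows are narrower than the WHO row. No rule states how rows combine or how codes match.

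The consequence depends on the reading. With own-row exact matching, diabetes and cardiovascular disease are under-ascertained as entry criteria and covariates, and N17-coded AKI in Beijing-coded records depends on the creatinine or text routes. With pooled prefix matching, only the AKI/AKD set remains in question.

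Either way the effect on cohort entry should be small, because hypertension and age above 60 also qualify. This assumes that most affected patients have at least one other risk factor, which is likely but not quantified in the protocol. AKI history is not a named covariate. Error in the diabetes and cardiovascular covariates mainly weakens the adjustment and does not by itself bias the arm comparison. The point is worth correcting because the protocol itself fixes these lists and the correction is cheap.

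**What to change.** Replace the three unlinked rows with one concept list per disease, and state that codes are matched by prefix on the WHO-row categories:

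- **Type 2 diabetes:** all E11 codes in every coding version.
- **Cardiovascular disease:** add I63 and I22 to both local rows, and I23, I24, I51.6 and I61 to the Beijing row.
- **AKI/AKD:** include N17 and the other WHO-row categories in the China and Beijing rows. Then make the three rows agree in Tables 2 and 3, either by adding N00, N10, N12 and N13 to the WHO row, labelled as AKD, or by removing them from the local rows.

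Add a sentence saying that the corrected lists define the entry criteria and the baseline covariates. The uncorrected lists should not be reused for the AKI or stroke components of the main outcomes.

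The cost is a table revision, a re-run of the database query, and small shifts in cohort and covariate counts. No new data or patients are needed.
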